### Study design

Prospective, multi-centric, non-randomized study. Study inclusion period will be four years, each patient will be followed for 2 years and study total duration will be 6 years. Study design is depicted in Fig. 1.

**Fig. 1 Fig1:**
[figure not shown]
Study Design

Investigators will receive an informative notice on OncoSNIPE study and will provide eligible patients with laboratory procedures.*Sampling*Initial samplingPrior to any treatment tumor biopsy and 10 ml of blood (2*2.5 mL RNA PAXgene tubes, 5 mL dry tubes) will be collected. Tumors biopsy will be collected in standard care for histologically proven breast, lung and PDAC patients with formalin-fixed paraffin-embedded (FFPE) standard procedure and PDAC-derived organoid will be produced for non-histologically proven pancreas cancer patients before the clinical study inclusion. RNA-seq and Exome-seq will be performed on tumor biopsy. Cytokine profile and RNA-seq will be performed on blood samples.Follow-upSample collection schedule will depend on treatment standard of care: 10 ml blood sample (2*2.5 ml RNA PAXgene tubes, 5 ml dry tubes) analysis will be collected at 2 months (T2) for pancreatic and lung cancer and 12 months (T12) for breast cancer. Cytokine profile and RNA-seq will be performed.Sample schedule will be maintained even if toxicity leads to treatment changes.Disease progressionIf disease progression is observed, blood and tumor biopsy will be collected: 10 ml blood (2*2.5 ml RNA PAXgene tubes, 5 ml dry tubes). Tumor biopsies will be collected in standard care for breast and lung cancer. RNA-seq and Exome-seq will be performed on tumor biopsies. Cytokine profile and RNA-seq will be performed on blood samples.Sample processingPAXgene tubes will be kept at RT (15–25 °C) at least 2 h and then placed at -20 °C 24 h to 72 h. Tubes will then be transferred at -80 °C until use.Blood samples collected in dry tubes will be kept for a maximum of 1 h at RT (15–25 °C). After centrifugation (1200 g, 15 min, RT) serum will be aliquoted (about 10 tubes of 250 µL) and will be store at -80 °C.PDAC-derived organoids were obtained from patients with unresecable tumors by Endoscopic Ultrasound Fine Needle Aspiration (EUS-FNA). Biopsies will be digested with Tumor Dissociation Kit (Miltenyi Biotec) at 37 °C for 5 min, then incubated with Red Blood Cell Lysis Buffer (Roche) and washed 2 times with PBS. The digested samples will be transferred into a tissue strainer 100 μm and will be placed into 12-well plate coated with 150 μl GFR matrigel (Corning). The samples will be cultured with Pancreatic Organoid Feeding Media (POFM) consisting of Advanced DMEM/F12 supplemented with 10 mM HEPES (Thermo-Fisher); 1 × Glutamax (Thermo-Fisher); penicillin/streptomycin (Thermo-Fisher); 100 ng/ml Animal-Free Recombinant Human FGF10 (Peprotech); 50 ng/ml Animal-Free Recombinant Human EGF (Peprotech); 100 ng/ml Recombinant Human Noggin (Biotechne); Wnt3a-conditioned medium (30% v/v); RSPO1-conditioned medium (10% v/v); 10 nM human Gastrin 1 (Sigma Aldrich) 10 mM Nicotinamide (Sigma Aldrich); 1.25 mM N acetylcysteine (Sigma Aldrich); 1 × B27 (Invitrogen); 500 nM A83-01 (Tocris); 10.5 μM Y27632 (Tocris). The plates will be incubated at 37 °C in a 5% CO_2_ incubator, and the media will be changed every 3 or 4 days.Sample analysisTumors analysis:FFPE tumors for breast and lung cancer will be analyzed by a pathologist to determine the percentage of tumor cell content. Only samples with more than 30% of cancerous cells and successful PDAC-derived organoids will be analyzed.DNA will be extracted using the Maxwell RSC DNA FFPE kit (Promega) according to the manufacturer’s protocol. DNA will be quantified using fluorometric assay with a Qubit device. RNA will be extracted using the Maxwell RSC RNA FFPE kit (Promega) according to the manufacturer’s protocol. RNA quality and quantity will be assessed by spectrophotometry with absorbance at 230, 260 and 280 nm.i.Exome analysis on tumor samplesTwo hundred nanograms of genomic DNA will be fragmented with a Covaris device to obtain fragments around 300 bp. Then, libraries will be constructed and captured by using SureSelect Human All Exon v6 kit (Agilent), following the manufacturer’s protocol. Paired-end (2 × 111 bases) sequencing will be performed on a NextSeq500 device (Illumina) as described previously (6–10) with a mean target coverage of 100X.ii.RNA sequencing on tumor samplesRibosomal RNA depleted RNA will be used for library preparation with the NEBNext Ultra II Directional RNA library prep kit for Illumina according to the manufacturer’s instructions (New England Biolabs). RNA sequencing will be performed on a NextSeq500 device (Illumina) as described previously (6;10–13). The libraries will be sequenced with paired-end 76–base pair ‘reads’ with a target of 30 million of reads per sample.b) Blood samples analysis:iii.RNA sequencing on blood samplesRNA from PAXgene blood samples will be extracted using the Maxwell RSC simply RNA blood kit (Promega) according to the manufacturer’s protocol. RNA quality and quantity will be assessed by spectrophotometry with absorbance at 230, 260 and 280 nm.Ribosomal and globin RNA depleted RNA will be used for library preparation with the NEBNext Ultra II Directional RNA library prep kit for Illumina according to the manufacturer’s instructions (New England Biolabs). RNA sequencing will be performed on a NextSeq500 device (Illumina). The libraries will be sequenced with paired-end 76–base pair ‘reads’ with a target of 30 million of reads per sample.iv.Cytokine profiling on blood samplesCytokines will be analyzed using the multiplex assay provided by Meso Scale Discovery MSD®. The principle of the multiplex assay resides on specific binding between unique linkers organized onto unique spot, which couples with specific biotinylated captures antibodies (developed by MSD®). Cytokines in the sample bind to the specific biotinylated capture antibodies. Then, detection antibodies conjugated with electroluminescent labels bind to the analyte to complete sandwich immunoassay. Once this step done, the QUICKPLEX SQ 120 (MSD®) applies a voltage to the microplate electrodes and the captured labels emit light. The instrument measures the emitted light from each spot, which is proportional to the analyte present in the sample and provide a quantitative measure.Bioinformatics analysisNGS (RNAseq and Exome libraries) quality control and preprocessing of FASTQ files are controlled to provide clean data for downstream NGS analysis (number of reads, length of the insert, duplication rate, percent of GC, coverage…). Before analysis, the library files are cleaned up by removing bad quality bases, unknown bases “N” and too short sequences, and by trimming artificial sequences such as adapters.**RNAseq analysis:** Sequenced data is mapped on the human genome, using the "hg19" version of the human genome and version 92 of the Ensembl database for annotation features. The mapping is performed by the STAR software with paired-end parameters. Through a double approach, we count genes and exons separately. The Htseq-count program is run two times, once for measuring the number of genes and the other for measuring the exons. The counting of both Exon and Gene data is intended to increase the mapping quality and the accuracy of the analysis. We perform a differential expression analysis (DE) considering potential genes/exons with the software R version 4.0.3 with a double-crossed analysis using both edgeR v3.32.0 and DESeq v1.30.0 packages. Results from both methods will be crossed to assure a better reliability.**Exome analysis:** Sequenced data will be mapped on the human genome, using the "hg19" version of the human genome and version 92 of the Ensembl database for annotation features. The mapping will be performed by the BWA software with paired-end parameters and the 'MEM' option due to the large size of the human genome and the need to allocate a large amount of RAM memory for the execution of the software. After mapping reads to the reference genome, the workflow will removed duplicates before variant calling to mitigate biases introduced by data generation steps such as PCR amplification. After that, base quality scores will be recalibrated, because the variant calling algorithms rely heavily on the quality scores assigned to the individual base calls in each sequence read. For variant calling, different softwares will be used to detect both SNVs (Single Nucleotide Variant) and InDels (Sequence Insertion or Deletion): Mutect2 and GATK HaplotypeCaller for SNVs detection, and GATK HaplotypeCaller and Pindel for InDels detection.

### Data collection

The following data will be collected during the study, at the time of inclusion and during medical follow-up: demographic and clinical data (age, sex, weight, height, performance status, SBR, …), medical history, date of diagnosis, 1^st^ and 2^nd^ lines of treatments, disease evaluation reports (biological, imaging,…), will be sent as a standard report from the laboratory in charge of these analysis. All data will be recorded in the CRF (CSOnline 7.0.204.3 ClinSight®).

### Sample size

PDAC axis:

The expected response rate at 2 months is 30%.The probability modelized is non response to treatment with the assumption of an area under the ROC (Receiver Operating Characteristic) curve (AUC, Area Under de Curve) between 80 and 85%, a number of 200 subjects, i.e. 60 responders and 140 resistants (non-responders) will allow us to reach a power between 82 and 100% to prove a difference of 0.10 to 0.15 points against a theoretical AUC of 0.70, with a unilateral alpha risk of 5%.

To get 200 assessable patients for PDAC axis, a total of 400 patients should be included to anticipate a rate of non-evaluable patients of 50%.

Patients not assessable for the pancreas axis will be replaced and are defined as follows: premature exit (death) from study before treatment, patient who received less than 2 treatment cycles, patient who left studies prematurely before carrying out the efficacy visit (2 months after the start of treatment) or progression and patient with unsuccessful PDAC-derived organoid development.b)Lung cancer axis:

The expected response rate at 2 months is 30%. The expected response rate at 2 months is 30%. The probability modelized is non response to treatment with the assumption of an area under the ROC curve (AUC) between 80 and 85%, a number of 200 subjects, i.e. 60 responders and 140 resistants (non-responders) will allow us to reach a power of between 82 and 100% to prove a difference of 0.10 to 0.15 points against a theoretical AUC of 0.70, with a unilateral alpha risk of 5%.

To get 200 assessable patients for lung cancer axis, a total of 260 patients should be included to anticipate a rate of non-evaluable patients of 30%.

Patients not assessable for the lung axis will be replaced and defined as follows: prematurely exit (death) from study before treatment, patient having received less than 2 treatment cycles, patient who left studies prematurely before carrying out the efficacy visit (3 months after the start of treatment) or progression (excluding patients always responding after 24 months of follow-up).iii)Breast cancer axis:

The expected response rate at 2 years is 50%. The probability modelized is non response to treatment with the assumption of an area under the ROC curve (AUC) between 80 and 85%, a number of 200 subjects, i.e. 100 responders and 100 resistants (non-responders) will allow us to reach a power of between 86 and 100% to prove a difference of 0.10 to 0.15 points against a theoretical AUC of 0.70, with a unilateral alpha risk of 5%.

To get 200 assessable patients for breast cancer axis, a total of 230 patients should be included to anticipate a rate of non-evaluable patients of 15%.

Patients not assessable for the breast axis will be replaced and defined as follows: prematurely exit (death) from study before treatment, patient having received less than 2 treatment cycles, patient who left studies prematurely before carrying out the efficacy visit (3 months after the start of treatment) or progression (excluding patients always responding after 24 months of follow-up).

Non-assessable patients will be replaced.

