### Study objectives and endpoints

The main objective of this study is to identify biomarkers of resistance to treatment in patients with triple negative or Luminal B breast cancer, locally advanced or metastatic non-small cell lung cancer or PDAC.

Analyses will be performed in each cohort independently. The primary endpoint will be a combinatory analysis of genomic, transcriptomic, clinical, medical images and immunological profile realized by ELISA and NGS (Next Generation Sequencing; Exome-seq, RNA-seq). Markers can be early or late biomarkers. The early markers will be markers present at baseline, the late markers will be the ones appearing during the follow-up. Resistance is defined as a tumoral nonresponse according to the RECIST (Response Evaluation Criteria In Solid Tumor) criteria or absence of Pathologic Complete Response (pCR).

The secondary objectives are to (i) identify therapeutic targets; (ii) determine the prognostic impact of the resistance markers on progression-free survival (PFS) and overall survival (OS),with PFS defined as the time between inclusion and progression (according to RECIST criteria or pCR) or death whatever the cause, and OS defined by the time between inclusion or death whatever the cause; (iii) identify the clinical, biological and/or genomic characteristics of long survivors (ie Patients who are still responding to the first line of treatment at the end of the 2-year follow-up.

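### The rule for replacing non-assessable patients depends on what happens after treatment starts, so some early treatment failures are removed from the set on which the primary AUC analysis is powered

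*Protocol article*

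**What the plan says.** The Sample size section plans 200 assessable patients per axis: 60 responders and 140 non-responders in PDAC and in lung, 100 and 100 in breast. For PDAC it claims "power between 82 and 100% to prove a difference of 0.10 to 0.15 points against a theoretical AUC of 0.70" at a one-sided 5% level; lung has the same figures, and breast has 86% to 100%. To reach 200 it plans 400, 260 and 230 inclusions, with anticipated non-evaluable rates of 50%, 30% and 15%.

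A patient is not assessable after leaving or dying before treatment. So is a "patient who received less than 2 treatment cycles, patient who left studies prematurely before carrying out the efficacy visit" (PDAC wording; lung and breast are almost the same). PDAC adds failed organoid development. In lung and breast the last clause continues "or progression (excluding patients always responding after 24 months of follow-up"). The section closes with "Non-assessable patients will be replaced".

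Study objectives and endpoints defines resistance as RECIST non-response or absence of pCR. It runs PFS from inclusion to "progression (according to RECIST criteria or pCR) or death whatever the cause". Study design has biopsy and blood taken before any treatment. Statistical analysis leaves the detail to a plan to be written before database lock.

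**The concern.** The modelled probability is non-response. A patient who starts treatment and progresses or dies after one cycle is a clear instance of it, and the pre-treatment samples needed for the early markers are scheduled for that patient. The rule nevertheless sets the patient aside and enrols another, who must last longer to count.

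The cycle criterion stands alone. The words on progression belong to the next item in the list, so documented progression does not rescue a patient with fewer than 2 cycles. A patient with at least 2 cycles who dies before the efficacy visit without documented progression may be lost as well.

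At stake is whether the AUC describes resistance in the patients enrolled, or only in those who survive early treatment. In lung and breast there is a further question: whether leaving progression-free before 24 months also makes a patient non-assessable.

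**Working it through.** **1. The plan's own power, to establish which set it rests on.** One-sample AUC test with binormal variance, non-response as the positive class:

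- a = 1.414 × Φ⁻¹(AUC), k = n(responders)/n(non-responders)
- Var = 0.0099 × exp(−a²/2) × [5a² + 8 + (a² + 8)/k] / n(non-responders)
- Power = Φ{(AUC − 0.70 − 1.645 × SE₀)/SE₁}

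PDAC and lung (140 non-responders, 60 responders), AUC 0.80: SE₀ = 0.0406, SE₁ = 0.0359, so (0.10 − 1.645 × 0.0406)/0.0359 = 0.92 and power is 82.2%. At AUC 0.85 it is 99.5%. Breast (100/100): 86.0% and 99.7%. These match the stated 82–100% and 86–100%, so the claimed power belongs to the assessable patients.

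**2. How many patients the rule sets aside.** On the planned inclusions: PDAC 400 − 200 = 200, lung 260 − 200 = 60, breast 230 − 200 = 30. These totals mix pre-treatment exits, organoid failures (PDAC), early failures and other early leavers. The article gives no breakdown.

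**3. Response rate if a share f of those set aside are early failures (f assumed).** Rate = responders/(200 + f × number set aside).

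| Axis | Planned | f = 10% | f = 25% | f = 50% |
|---|---|---|---|---|
| PDAC | 30% | 60/220 = 27.3% | 60/250 = 24.0% | 60/300 = 20.0% |
| Lung | 30% | 60/206 = 29.1% | 60/215 = 27.9% | 60/230 = 26.1% |
| Breast | 50% | 100/203 = 49.3% | 100/207.5 = 48.2% | 100/215 = 46.5% |

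**4. AUC.** The AUC over all non-responders is the weighted mean of the AUCs for kept and dropped non-responders against the same responders. Take 0.80 for the kept, f = 50%, and 0.60 to 0.90 for the dropped (all assumed):

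- PDAC: (140 × 0.80 + 100 × 0.60)/240 = 0.717, up to (112 + 90)/240 = 0.842
- Lung: (112 + 30 × 0.60)/170 = 0.765, up to (112 + 27)/170 = 0.818
- Breast: (80 + 15 × 0.60)/115 = 0.774, up to (80 + 13.5)/115 = 0.813

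If dropped and kept failures have the same marker distribution, the AUC stays at 0.80.

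A latent-resistance simulation (marker–latent correlation 0.65, 400,000 patients) shows the same dependence. The full AUC is 0.81. Removing exactly the most resistant 10% or 20% gives 0.79 or 0.77, where the 60/140 design has about 74% or 53% power. Removing the same number of non-responders at random leaves 0.81.

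**5. PFS, only if it were run on the assessable set.** Assume 24-month PFS of 50%, exponential event times and non-informative exponential dropout. With 15% leaving progression-free before 24 months, 45.3% have an event and 39.7% reach 24 months. Deleting the leavers gives 0.3974/0.85 = 46.8% (10% leaving: 47.9%; 30%: 42.6%). Dropping early failures acts the other way: removing 10% of patients, all early failures, turns 50% into 0.50/0.90 = 55.6%.

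**The case against.** The strongest reply is that the rule sits under Sample size and governs who is replaced, while analysis sets are deferred to a later plan. For PFS and OS this stands. A reader might infer that censored follow-up is deleted and PFS comes out too short. The article nowhere restricts PFS or OS to assessable patients; it runs both from inclusion. Even on the restricted set, the two parts of the rule would pull in opposite directions. For the primary AUC the reply does not stand, because the stated power belongs to that set and replacement operates during recruitment.

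Four further limits stand:

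- Not every early failure goes. A patient with at least 2 cycles and documented progression before the visit is kept.
- The 50%, 30% and 15% rates do not measure loss of failures. They include exits before treatment and, in PDAC, organoid failures.
- A reader might infer that the AUC is pulled towards the 0.70 null. That follows only if the dropped patients are those the marker separates best. The range in step 4 runs both ways and includes no change.
- The 24-month reading is not the only one. The clause could mean leaving before either the visit or progression had occurred, so that completing the visit suffices. The parenthesis about 24-month responders has little purpose on that reading, and the breast response rate is given at 2 years, so the stricter reading is the more natural. It remains ambiguous.

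Counting every missing response as non-response would go too far: withdrawals for toxicity or logistics would enter the resistant class without a tumour assessment.

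**Conclusion.** The point holds for the primary analysis. In all three axes assessability depends on post-baseline course, and treated patients with fewer than 2 cycles are replaced even when the reason is progression or death. The 200 assessable patients are therefore partly selected on the outcome being modelled.

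The consequence is a risk of bias in the AUC of unknown direction and size, and a conclusion confined to patients who get through early treatment. The PDAC response rate of 27% to 20% instead of 30% is a sensitivity range resting on an assumed 10% to 50% share of early failures; response rate is a planning input here, not an endpoint. The lung and breast clause needs clarifying. Bias in PFS would follow only if PFS were run on the assessable set, which the article does not say.

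**What to change.** 1. In the primary analysis, count documented progression (including clinical) or death after treatment start and before the efficacy visit as non-response, whatever the number of cycles received.
2. Limit replacement to patients who never start treatment, have no usable baseline sample or organoid, or leave alive and progression-free with no response assessment. Report their numbers by reason. Use missing-as-non-response only as a sensitivity analysis.
3. Reword the lung and breast clause so that a patient who completed the efficacy visit is assessable. State that all included patients stay in PFS and OS, with progression-free leavers censored.
4. Keep the present assessable set as a sensitivity analysis.

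The cost is rewording the assessability definition and the analysis sets; fewer replacements should be needed. The downside is that some patients enter the primary analysis with little treatment exposure, which item 4 addresses.

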**Methods:**

Multicentric, interventional study with the primary objective to identify early and / or late markers of resistance to treatment, in 600 adult patients with locally advanced or metastatic triple negative or Luminal B breast cancer, non-small-cell lung cancer or pancreatic ductal adenocarcinoma. Patients targeted in this study have all rapid progression of their pathology, making it possible to obtain models for evaluating markers of early and / or late responses over the 2-year period of follow-up, and thus provide the information necessary to understand resistance mechanisms. To explore the phenomena of resistance, during therapeutic response and / or progression of the pathology, we will use a multidisciplinary approach including high-throughput sequencing (Exome-seq and RNAseq), clinical data, medical images and immunological profile by ELISA. Patients will have long-term follow-up with different biological samples, at baseline (blood and biopsy) and at each tumoral evaluation or tumoral progression evaluated by medical imaging. Clinical data will be collected through a dedicated Case Report Form (CRF) and enriched by semantic extraction based on the French ConSoRe (Continuum Soins Recherche) initiative, a dedicated Semantic Clinical Data Warehouse (SCDW) to cancer.

The study is sponsored by Oncodesign (Dijon, France) and is currently ongoing.

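### Lung inclusions are inflated as 200 × 1.30 = 260 instead of 200/0.70 = 286, with the same slip on a minor scale for breast (230 instead of 236), so planned recruitment is understated

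*Protocol article*

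**What the plan says.** The Sample size section of the protocol article sets a target of 200 assessable patients on each of three axes and inflates each target for non-evaluable patients:

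- PDAC: "a total of 400 patients should be included to anticipate a rate of non-evaluable patients of 50" per cent.
- Lung, with the same target: "a total of 260 patients should be included to anticipate a rate of non-evaluable patients of 30" per cent.
- Breast, again with the same target: "a total of 230 patients should be included to anticipate a rate of non-evaluable patients of 15" per cent.

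Power is stated for the 200 patients. For lung (60 responders, 140 non-responders) the design "will allow us to reach a power of between 82 and 100" per cent. For breast (100 and 100) the range is 86% to 100%. Both ranges refer to a true AUC of 0.80 to 0.85 tested against 0.70 at a one-sided 5% level.

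The section defines non-assessable patients for each axis, says each time that they are replaced, and ends with the general rule "Non-assessable patients will be replaced". The Methods paragraph of the abstract describes the study as being "in 600 adult patients with locally advanced or metastatic triple negative or Luminal B breast cancer", among the other tumour types, and does not say whether these 600 are included or assessable.

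**The concern.** A non-evaluable rate is the share of included patients who cannot be analysed. The assessable target must therefore be divided by one minus that rate. Multiplying by one plus the rate always gives too small a number, and the gap widens as the rate rises. The lung and breast totals match the multiplication exactly, while the PDAC total matches the division. One section thus applies two incompatible rules to the same kind of quantity.

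What is at stake is the recruitment target. Someone who plans lung recruitment on 260 will, at the protocol's own rate, need about 26 more inclusions before 200 patients can be analysed. If recruitment were instead closed at 260, the analysis would rest on fewer patients than the stated power assumes.

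**Working it through.** **Inputs** (all from the Sample size section): assessable target 200 per axis; non-evaluable rate d = 0.50 (PDAC), 0.30 (lung), 0.15 (breast); stated inclusions 400, 260, 230; null AUC 0.70; alternatives 0.80 and 0.85; one-sided 5%.

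**1. Which rule gives the stated totals?**

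| Axis | Stated | 200/(1 − d) | 200 × (1 + d) |
|---|---|---|---|
| PDAC | 400 | 200/0.50 = 400 | 200 × 1.50 = 300 |
| Lung | 260 | 200/0.70 = 285.7, so 286 | 200 × 1.30 = 260 |
| Breast | 230 | 200/0.85 = 235.3, so 236 | 200 × 1.15 = 230 |

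PDAC follows the division only. Lung and breast equal the multiplication exactly.

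**2. What the stated totals deliver at the stated rates**

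- PDAC: 400 × 0.50 = 200.
- Lung: 260 × 0.70 = 182, which is 18 short (9%).
- Breast: 230 × 0.85 = 195.5, which is 4.5 short (about 2%).

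The lung total suffices only if the rate is at most 1 − 200/260 = 23.1%, and the breast total only if it is at most 1 − 200/230 = 13.0%.

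**3. Total inclusions**

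Stated: 400 + 260 + 230 = 890. Corrected: 400 + 286 + 236 = 922. The difference is 26 + 6 = 32.

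**4. Does the stated power belong to 200 assessable patients?**

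The article does not name its power method. I used a one-sample normal test of the AUC with the binormal (Obuchowski) variance:

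Var(AUC) = 0.0099 · exp(−A²/2) · [(5A² + 8) + (A² + 8)/k] / n₁, with A = 1.414 · Φ⁻¹(AUC), n₁ non-responders, n₀ responders and k = n₀/n₁.

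Power = Φ[(AUC₁ − 0.70 − 1.645 · SE₀)/SE₁], where SE₀ is taken at 0.70 and SE₁ at the alternative.

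- Lung and PDAC, 140/60, AUC 0.80: SE₀ = 0.0406, SE₁ = 0.0359, so (0.10 − 1.645 × 0.0406)/0.0359 ≈ 0.92 and power is 82.2% (stated 82%). At AUC 0.85 it is 99.5%.
- Breast, 100/100, AUC 0.80: SE₀ = 0.0381, SE₁ = 0.0346, so the argument is about 1.08 and power is 86.0% (stated 86%). At AUC 0.85 it is 99.7%.

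The plan's power figures reproduce at 200 assessable patients per axis.

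**5. Power if inclusion stopped at 260 and 230 without further replacement**

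- Lung, 182 assessable split 127/55: SE₀ = 0.0425, SE₁ = 0.0376, argument about 0.80, power 78.8% at AUC 0.80 and 99.2% at 0.85.
- Breast, 195 assessable split 98/97: SE₀ = 0.0386, SE₁ = 0.0350, argument about 1.05, power 85.2% at AUC 0.80 and 99.7% at 0.85.

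**6. With replacement**

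Including patients until 200 are assessable takes an expected 200/(1 − d) inclusions. This gives the same 286 and 236 (rounded up), so replacement leads to the corrected totals and does not justify the stated ones.

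**The case against.** The strongest defence is the replacement rule. The operative target is 200 assessable patients per axis, no cap at 260 or 230 is stated, and at 200 the stated power is right. This stands. A reader might infer that the lung and breast analyses will be underpowered, but the article does not support that: the loss arises only if inclusion ends at the stated totals. Even then it is about 3 points for lung and under 1 point for breast, at the lower end of the planned AUC range only.

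The breast error is also small. Six patients in 236 is 2.5%, well within the uncertainty of a 15% planning rate. That stands too; breast matters mainly because it shows the same rule.

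It could be argued that the rate was meant relative to the assessable number, so that 30% means 60 extra per 200. The PDAC axis rules this out as a common convention, since it would then need 300 and not 400.

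A reader might also set the abstract's 600 against 890 inclusions and call it a contradiction. The article does not show one: 600 is exactly 3 × 200, so the natural reading is assessable patients. The figure lacks a label. It is also unrelated to the inflation rule, since correcting the rule raises the total to 922, further from 600. Nor can anything be inferred about budgets, which the article does not contain.

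None of this rescues 260 as the number of inclusions expected to give 200 assessable patients at a 30% non-evaluable rate.

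**Conclusion.** The lung total is wrong as written, by the section's own rate and by the rule it applies to PDAC: 286 is needed where 260 is stated, an understatement of 26. Breast has the same slip on a minor scale, 236 against 230. The assessable target of 200 per axis and the power attached to it are sound.

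The main consequence is an understated recruitment need, 32 inclusions over the whole study. A loss of power is conditional on the totals acting as caps, which the article does not say. The recruitment figures assume that the stated non-evaluable rates hold. The power figures also assume the binormal variance, which reproduces the plan's own values, and unchanged responder proportions among assessable patients. The unlabelled 600 is a separate and minor matter of clarity.

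**What to change.** In the Sample size section:

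- Restate inclusions as 286 for lung (200/0.70) and 236 for breast (200/0.85), keep 400 for PDAC, and give the total of 922.
- State how replacement relates to these totals: whether replaced patients are counted within them, and whether inclusion continues until 200 are assessable on each axis.
- If 260 and 230 are in fact caps, keep them but restate the expected assessable numbers as 182 and 195, with power at AUC 0.80 of about 79% and 85%.

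As a separate clarification in the abstract, label 600 as assessable patients (3 × 200) and give the planned inclusions beside it.

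The cost is a few corrected figures and one added sentence. The assessable targets, the error rate and the analysis do not change. Where replacement is already intended, the revised totals only state the recruitment that the plan implies.
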